# Healthy Eating and Active Living for Diabetes-Glycemic Index (HEALD-GI): Protocol for a Pragmatic Randomized Controlled Trial

**DOI:** 10.2196/11707

**Published:** 2019-03-06

**Keywords:** glycemic index, randomized controlled trial, type 2 diabetes mellitus

## Abstract

**Background:**

Rigorous evidence is needed regarding the best approach for increasing the uptake of Diabetes Canada’s evidence-based recommendations to include low-glycemic index (GI) foods in daily meal planning as an effective dietary self-care strategy for glycemic control among people with type 2 diabetes (T2D).

**Objective:**

This study aims to present the study design and baseline data from the Healthy Eating and Active Living for Diabetes-Glycemic Index (HEALD-GI) trial, which was designed to evaluate the effectiveness of an enhanced GI-targeted nutrition education on GI-related knowledge and mean daily GI among adults with T2D in Edmonton, Alberta.

**Methods:**

We used a pragmatic randomized controlled trial design and allocated 67 adults (aged ≥18 years) with T2D living in Edmonton, Alberta, Canada, to a control group that received standard printed copies of Canada’s Food Guide and Diabetes Canada’s GI resources or to an intervention group that received the same materials, plus a customized Web-based platform with 6 self-directed learning modules and print material. Each module included videos, links to reliable websites, chat rooms, and quizzes. Evidence-based GI concept information included GI values of foods and low-GI shopping, recipes, and cooking tips by a registered dietitian. In addition, support through email, text messaging (short message service), phone calls, or postal mail was provided to reinforce participants’ learning. The primary outcome, average dietary GI, was assessed using 3-day food records. Additional measures including GI knowledge and self-efficacy, glycated hemoglobin (HbA_1c_), lipids, systolic blood pressure, body mass index (BMI; weight, height), waist circumference, and computer proficiency were assessed at baseline and at 3-month postintervention.

**Results:**

Between November 2017 and February 2018, we contacted adults (aged ≥18 years) with T2D living in Edmonton, Alberta, screened and recruited eligible participants into the study. All data collection ended in June 2018. Overall, 64% (43/67) participants were males; mean age was 69.5 (SD 9.3) years, with a mean diabetes duration of 19.0 (SD 13.7) years. Mean BMI was 30.1 (SD 5.7) kg/m^2^, and mean HbA_1c_ value was 7.1% (SD 1.2%). Data analysis was completed in December 2018.

**Conclusions:**

The GI concept is often difficult to teach. The HEALD-GI study aims to provide evidence in support of an alternative approach to translating the GI concept to adults with T2D. Findings from this study may help registered dietitians to better disseminate low-GI dietary recommendations using efficient and cost-effective, patient-centered approaches. Furthermore, evidence generated will contribute to addressing some of the controversies regarding the clinical usefulness of the GI concept.

**International Registered Report Identifier (IRRID):**

DERR1-10.2196/11707

## Introduction

Increasing prevalence of type 2 diabetes (T2D) remains a major public health challenge with adverse effects for individuals and health care systems globally. Currently, diabetes affects approximately 7.3% of Canadians, and the prevalence has been projected to rise to about 10% by 2020 [1]. Health outcomes for individuals with diabetes, however, largely depend on their ability to self-manage the disease. Lifestyle interventions including healthy eating, physical activity, and smoking cessation, which enhance the acquisition of knowledge, skills, resources, and support to boost self-efficacy for day-to-day living, are, therefore, important for T2D management and prevention of long-term complications [2,3].

Healthy eating remains a key strategy for diabetes self-management, and dietary carbohydrates constitute one aspect of the diet with significant influence on blood glucose control. Different types and quantities of carbohydrates have been shown to impact blood glucose concentration differently [4,5]. This property of foods, referred to as glycemic index (GI), is used to rank how quickly a given dietary carbohydrate raises blood glucose concentration immediately following a meal [4]. Using GI and the portion size of a given food, glycemic load (GL), a composite measure of carbohydrate quality and quantity, can be calculated to predict blood glucose response to a specific type and amount of a dietary carbohydrate [6]. Consuming low-GI foods is beneficial for metabolic control in diabetes management [7]. Adopting a low-GI dietary pattern as part of a healthy eating lifestyle has been shown to markedly reduce cardiovascular risk factors (eg, total cholesterol, high-density lipoprotein); improve glycemic control, postprandial glycemia, and beta cell function; and decrease the need for antihyperglycemic agents among patients with diabetes [8-18]. Outlining effective approaches to promoting the concept of low-GI intake among individuals with T2D has been problematic. Hence, examining effective modes of delivery is necessary to support one aspect of T2D.

Effective and widespread use of information technologies (ITs), including the internet and mobile-based tools, is revolutionizing the traditional approaches for engaging, educating, and empowering individuals with chronic diseases such as diabetes [19,20]. Increasing use of IT by diverse audiences, occasioned by low-cost Web- and mobile-based tools may, therefore, offer viable prospects for promoting swift and cost-effective GI concept education and support among people with T2D. Features of modern IT tools such as websites, chat rooms, social networking sites (eg, Facebook), and short message service (SMS) text messaging apps allow creation and exchange of health-promoting information and enable individuals to interact with other users who share connections with them [21,22]. Properly designed and managed websites can serve as credible sources of evidence-based GI-targeted messages. Websites enable integration and presentation of text, graphics, or audiovisuals on one platform, while chat rooms and emails facilitate engagement between users and health professionals in addressing pertinent issues [23]. Furthermore, chat rooms provide Web-based social forums for peer group discussions, exchange of ideas, encouragement, and support [24,25].

Knowledge gaps exist between GI concept clinical guidelines and their translation to adults with T2D in Canada due to debates over clinical utility of GI, inconsistencies in teaching the GI concept by registered dietitians [26,27], and limited patient-dietitian interactions [28]; these limit patients’ knowledge and skills for uptake of GI dietary behavior. Patients lose out on the additional benefits of improving carbohydrate quality by consuming healthy, low-GI foods as part of healthy eating strategy for diabetes self-management. Hence, this study aims to examine the effectiveness of Web-based, GI-targeted nutrition education on dietary behavior and intakes among adults with T2D. We hypothesize that after 3 months, adults with T2D who were randomized to receive Web-based, GI-targeted nutrition education will consume a lower-GI diet and show improved glycemic control compared with a control group. Findings from this study will help determine whether, and how, current approaches to disseminating dietary recommendations pertaining to GI concept could be improved for better uptake using alternative, efficient, and cost-effective patient-centered approaches to nutrition self-care. Furthermore, the outcomes of this study will add to the body of evidence regarding the GI concept.

## Methods

### Study Design: Setting, Recruitment, Ethical Considerations, and Intervention

#### Setting and Population

Adults (aged ≥18 years) living in Edmonton, Alberta, Canada, with T2D and currently enrolled in the Alberta’s Caring for Diabetes (ABCD) cohort study [29] constituted the target population for this study. The ABCD cohort study [29] was designed to explore different aspects of diabetes care and the development of complications among individuals with T2D in Alberta. The ABCD cohort enrolled 2040 participants between 2012 and 2013 from all over the province of Alberta at inception and provided a suitable eligible population from which to draw participants for this intervention. The characteristics of the ABCD cohort have been reported elsewhere [29].

#### Inclusion and Exclusion Criteria

The inclusion criteria were as follows: individuals aged ≥18 years identified as having T2D and currently enrolled in the ABCD cohort study; able to read, understand, and converse in English; and willing to provide informed consent. For practical considerations, we prescreened all cohort participants living in Edmonton for enrollment in the intervention. Based on postal codes, 745 cohort participants who participated in the year 1 ABCD survey lived in Edmonton. However, due to relocation and mortality-related attrition, we invited only 485 ABCD cohort participants living in Edmonton between July 2017 and October 2017 to participate. Those who responded were screened for eligibility and subsequent recruitment into the study between November 2017 and February 2018. Those taking exogenous insulin and having physiological or medical conditions that interfere with usual digestive functions were excluded.

#### Participants Screening Procedures

We sent letters explaining details of the study to all eligible participants, asking them to contact the study staff if they were interested in participating in this study. We performed detailed prescreening over the phone to determine full eligibility once we received responses from those invited to participate. A maximum of 2 telephone contacts were made to remind eligible individuals who did not contact the research staff after 2 weeks of expressing their interest in participating in the study. We invited eligible participants to complete baseline anthropometry, biochemical, clinical, and dietary data collection at the Human Nutrition Research Unit located within the Alberta Diabetes Institute at the University of Alberta. A trained dietitian and registered nurse with data collection experience collected anthropometric data and relevant clinical measures using point-of-care instruments (DCA Vantage, Cholestech LDX, and BPTru).

#### Ethical Considerations

The University of Alberta and Athabasca University Health Research Ethics Boards reviewed and approved the study protocol. In line with research ethics requirements, all participants received adequate information about the study and had the opportunity to ask questions. We obtained written informed consent from participants prior to obtaining any study measurements after providing them an explanation of (1) the purpose of the study; (2) the allocation process; (3) the use of data and the means of assuring confidentiality; (4) voluntary participation and the participants’ right to withdraw from the study at any time; and (5) any potential harm that could occur as a result of the intervention.

### Randomization and Treatment Allocation

Using a pragmatic randomized trial design, we randomly allocated 67 eligible participants drawn from the ABCD cohort [29] who provided informed consent and completed baseline anthropometry, clinical, and dietary measurements to either the usual care or to intervention in a 1:1 ratio using a computer-generated allocation sequence (Stata SE 12.1; StataCorp) [30]. Allocation sequence and group assignments were generated centrally and enclosed in sequentially numbered and sealed envelopes. A statistician not involved with other aspects of the trial performed all randomization-related procedures.

#### Usual Care

Study participants allocated to the usual care (control arm) received standard printed copies of Canada’s Food Guide and Diabetes Canada (formerly Canadian Diabetes Association) GI resources in line with current Diabetes Canada Clinical Practice Guidelines [31,32]. The control group did not receive extra support aimed at increasing knowledge or skills for daily consumption of low-GI foods.

#### Enhanced Glycemic Index-Targeted Nutrition Education

Participants (n=33) allocated to the enhanced low-GI education intervention group received the same information as the control group in addition to vetted, evidence-based, learner-centered, low-cost, and actionable low-GI messages delivered through a Web-based platform with chat rooms, customized videos featuring a registered dietitian, and print material. Based on individual preference and needs, we provided additional support through email, SMS text messages, phone calls, or mail to reinforce participants’ learning. The GI concept and content of this intervention were in line with current Diabetes Canada Clinical Practice Guidelines as well as T2D patients’ suggested content and preferred modes of learning GI information [16,25]. The intervention website was managed by a trained research assistant who also moderated chat room discussions under the supervision of coinvestigators: KS, a registered dietitian and researcher, and [name] and [name], who also possess extensive research experience.

Participants received brief tutorials on website log-in, navigation, and usage during baseline data collection, which was reinforced at first log-in with a short video introduction to the program. The video emphasized the importance of low-GI eating and summarized the various aspects of the intervention. Those allocated to the intervention group covered a total of 6 modules over 12 weeks. These modules were aimed at enhancing knowledge and skills for improved GI dietary behavior change. Each module included customized videos featuring a registered dietitian, links to reliable websites, chat rooms for social support, and quizzes. Evidence-based GI content included GI values of foods; low-GI shopping, recipes, and cooking tips; and advice for eating out. Participants received a new module every 2 weeks. Specific topics covered in these modules included (1) general healthy eating for diabetes patients; (2) summary of the GI concept; (3) identifying, choosing, and shopping low-GI foods; (4) low-GI recipes, menus, and meal planning; (5) guidelines for eating out and snacking; and (6) GI concept and general diabetes self-management and healthy lifestyles. Participants were encouraged to outline and track personal, easily achievable goals that could enhance their GI knowledge and skills under each module. For example, in module 3, a participant could set a simple goal to learn how to identify low-GI versions of foods that he or she usually consumed. We delivered each module through the intervention website using user-friendly text, graphical displays, and module summary videos. All videos were developed in line with Canada’s Food Guide and Diabetes Canada Nutrition Therapy Clinical Practice Guidelines-based GI recommendations [31,32] to teach participants “hands-on” application of GI to daily meal planning.

To sustain enthusiasm, participants were granted access to subsequent modules at the end of the preceding module on the first day of each 2-week cycle; this was accompanied with electronic reminders delivered through email or SMS text message based on participants’ choosing. Participants responded to short quizzes meant to bolster key GI principles and lessons learned. Chat rooms were activated for each module to enable participants to share experiences in the form of success stories, challenges, and tips that enhance a sense of community for social support among participants. The chat room forum was monitored, and timely responses were provided to questions and concerns of participants. In addition, we provided weblinks to the international tables of GI and GL values of foods [33] and additional evidence-based information on GI concept as well as general diabetes self-management and healthy lifestyles. A review of similar Web-based studies has shown that interventions that provide interactive elements such as the following have been effective at generating and sustaining participants’ interest and exposure to Web-based interventions: (1) quizzes, searchable database, audio or video; (2) counselor support through counselor-led chat sessions, email, or phone contacts; (3) peer support through Web-based discussion forums or chats; and (4) regular updates of information on intervention websites [34].

Participants in the enhanced GI education arm also received copies of “The Shopper’s Guide to GI Values: the Authoritative Source of Glycemic Index Values for More Than 1,200 Foods” [35] in line with T2D patients’ preference for print-based material as a source GI information [25]. Briefly, the Shopper’s Guide, which was recommended to participants seeking to know more about GI in a previous study [36], is a lightweight, handy book coauthored by expert GI research scientists. It contains GI values of over 1200 foods arranged by categories to help identify healthier low-GI carbohydrate alternatives using handy household measures. The Shopper’s Guide is updated regularly and has comprehensive data on carbohydrates per serving and GL, a shopping list of low-GI essentials, ideas for gluten-free meals, facts about sugar and sweeteners, and tips for everyday meals and dining out. Furthermore, the Shopper’s Guide provides links to supplementary resources with reliable, evidence-based GI information [35].

In addition to the website and the Shoppers Guide [35], participants in the intervention arm were offered periodic emails, SMS text messages or telephone calls, or postal mail prompts to visit the website and/or use the print materials to acquire more GI knowledge as per individual preference. Participants were encouraged to use these mediums to seek assistance regarding specific personal dietary issues, which they may not want to post in the chat room discussion section of the website.

### Assessment of Study Outcomes

#### Primary Outcome

Our primary outcome measure was GI-related dietary behavior change and intake, measured using a 3-day food record.

#### Dietary Assessment, Glycemic Index, and Glycemic Load Estimation

Daily dietary intake was assessed for all participants at baseline and at 3 months using a 3-day food record. The 3-day food records are valid and reliable for capturing dietary behavior change by asking participants to record their food consumption as they eat [37]. All participants were asked to record, in as much detail as possible, descriptions of foods and beverages consumed over a 3-day period (ie, 2 weekdays and 1 weekend day). Participants were given further instructions on how to fill out the 3-day food record. Color photographs were provided to assist participants with estimating and recording appropriate portion sizes of foods and beverages they consumed in the 3-day food record logbooks. Pictures showing sample portions sizes of foods measured against items including a finger, palm of a hand, and a hockey puck were included and participants were encouraged to choose photographs that best represented their portion sizes or specify whether they consumed more or less. Mean daily food consumption and nutrient intake were estimated using the Food Processor Diet Analysis and Fitness Software (ESHA Research) at baseline and 3 months using the Canadian nutrient file.

All carbohydrate-containing foods identified from the 3-day food records were assigned GI values corresponding to the best geographic and botanical matches in the published International Table of Glycemic Index and Glycemic Load Values [33,38] or the updated University of Sydney Web-based database [39,40]. GI values were averaged for foods having more than one GI value from very similar matches. As the International Table and the University of Sydney Web-based databases do not provide an exhaustive entry of glycemic data for every food, the instances where foods could not be matched directly to those in the International Tables or Web-based database, GI values were calculated from the estimated GL [39] or matched to listed foods with similar characteristics (ingredients, composition, and physical properties) based on all information available to [name], a trained dietitian, and from his subjective experience and knowledge of foods [41-43]. As recommended [41,43,44], daily average GI and GL was calculated for all carbohydrate-containing foods identified from the 3-day food records using published international GI tables [33,38] (Figure 1).

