### Statistical Analysis, Power, and Sample Size Rationale

#### Statistical Analysis

Change in the mean daily GI of dietary carbohydrates from baseline to 3 months will be used as our primary effectiveness measure for improved low-GI knowledge and application. Descriptive statistics will be computed for all variables to determine the nature of the data and to test for normality assumptions. Changes in outcomes will be assessed using repeated-measures 2-way analysis of covariance. Potential sociodemographic and clinical factors associated with enhanced GI learning will be evaluated using generalized linear mixed-model analysis. Treatment condition, baseline scores, participant characteristics (eg, sex, education, and income), and computer proficiency that may be significantly related to outcomes will be controlled for. All data will be analyzed using Stata SE 12.1 (StataCorp).

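### Foods without a direct glycemic index (GI) match may be valued by one dietitian's judgement with no stated masking to arm, which leaves part of the primary outcome open to arm-related coding bias

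*Protocol article*

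**What the plan says.** The protocol article names the primary outcome twice. Under Primary Outcome: "Our primary outcome measure was GI-related dietary behavior change and intake, measured using a 3-day food record". Under Statistical Analysis: "Change in the mean daily GI of dietary carbohydrates from baseline to 3 months will be used as our primary effectiveness measure".

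The section Dietary Assessment, Glycemic Index, and Glycemic Load Estimation describes how each food gets its value.

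- **Default route.** Carbohydrate foods "were assigned GI values corresponding to the best geographic and botanical matches in the published International Table of Glycemic Index and Glycemic Load Values", or in a web database. Where several close matches exist, "GI values were averaged for foods having more than one GI value from very similar matches". Neither sentence says who does this.
- **No direct match.** "GI values were calculated from the estimated GL [39] or matched to listed foods with similar characteristics". The similarity criteria are ingredients, composition and physical properties, and the judgement draws on all the information that one trained dietitian has "and from his subjective experience and knowledge of foods".

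The article does not say whether this step was masked to arm or visit. Its only statement of independence is under Randomization and Treatment Allocation: "A statistician not involved with other aspects of the trial performed all randomization-related procedures". That protects allocation, not outcome coding.

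**The concern.** Mean daily GI is built food by food, so whoever values an unlisted food sets part of the primary outcome. The article gives that task to one person, calls the judgement subjective, and sets no limit on the information he may use.

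Participants cannot be blinded to a web-based education program, and their food records can carry traces of it. The section on the enhanced education says that the intervention arm was taught to identify low-GI versions of usual foods and was given a guide to more than 1200 GI values. A coder who reads a whole 3-month record could guess the arm without seeing a label.

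If judgement then leans one way in one arm, the same food can receive different values in the two arms, and the difference passes into the estimated effect. A larger sample does not remove this error.

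**Working it through.** **1. The plan's own figure.** Power and Sample Size Rationale gives a difference of 5 GI units, an SD of 4 to 5 (5 for d = 1), two-sided alpha 0.05, power 0.90, 21 per arm, 30% attrition and 67 enrolled.

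- n per arm = 2 × (1.960 + 1.282)² × (5/5)² = 21.0. The unrounded value is just above 21, so strict rounding up gives 22 per arm (44 in total) against the stated 42.
- Power at 21 per arm is 0.900 by the normal formula and 0.885 by the exact t test.
- Expected completers are 67 × 0.70 = 46.9, about 23 per arm.

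The sample size reproduces to within two participants, and the coding point does not affect it.

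**2. Which coding errors matter.** Figure 1, with the GI formula, is not shown, so I assume that mean daily GI is weighted by carbohydrate. Let f be the share of carbohydrate coded by judgement, taken as equal across arms and visits. Let b be the mean coding error on those foods in the intervention (I) or control (C) arm, at baseline (0) or 3 months (3).

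Bias in the difference in change = f × [(b_I3 − b_I0) − (b_C3 − b_C0)]

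- Error equal in all four cells gives 0.
- A lean by visit alone (b_I3 = b_C3 and b_I0 = b_C0) gives 0.
- A lean L in one arm at 3 months only gives f × L. This is the case that matters most.
- A lean L by arm, equal at both visits, cancels from a simple difference in changes. The plan also controls for baseline scores. With a baseline slope β below 1, f × L × (1 − β) then remains.

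**3. Size under assumed inputs.** The documents give neither f nor L, so every value of f and L below is an assumption. Shift = f × L.

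- 0.10 × 2 = 0.2 units, and 0.2/5 = 4% of the target
- 0.10 × 3 = 0.3 units (6%)
- 0.20 × 5 = 1.0 unit (20%)
- 0.40 × 5 = 2.0 units (40%)
- 0.30 × 10 = 3.0 units (60%)

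**4. Effect on the test when there is no true difference.** This uses the noncentral t with 23 per arm, two-sided alpha 0.05, and the plan's SD of intake as the SD of the comparison.

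| Shift (GI units) | Rejection rate, SD 5 | Rejection rate, SD 4 |
|---|---|---|
| 0.2 | 0.052 | 0.053 |
| 1.0 | 0.102 | 0.132 |
| 2.0 | 0.264 | 0.382 |
| 3.0 | 0.512 | 0.701 |

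A shift of 1 unit about doubles the nominal error at SD 5. A shift of 0.2 units is negligible.

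**The case against.** The strongest reply is that the article is silent on masking and does not say that it was absent. A journal article condenses a fuller protocol, and coder masking is a detail that a fuller document or coding manual may hold. A reader might infer that the dietitian knew the arm. The documents do not show that: the coder's name is removed, he cannot be tied to any other role, and nothing says that he saw the allocation. The wording about available information may mean information on the food only. What remains is that the article describes this step in some detail, makes it subjective and single-handed, and puts no limit on the information used. A better procedure can be set against the one described.

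A reader might also infer that every GI value rests on this dietitian. The text ties his judgement to foods without a direct match. Even there, calculation from estimated glycemic load is the other route, and the matching has stated criteria and cited methods. The default matching and the averaging also call for choices, but no coder is named for them. The point is therefore limited to foods not directly matched.

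Two other inferences fail. A lean by visit alone cancels between arms, as shown above. Coding is also not the only step that could be masked: entry of records into the nutrient software and the statistical analysis could be masked too.

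Finally, the magnitudes depend on guesses and run from 4% to 60% of the target. That is a fair criticism. They show how the bias would act, not how large it is likely to be.

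**Conclusion.** The concern holds in a limited form. For foods without a direct match, part of the primary outcome may rest on one dietitian's judgement, and the article states no masking of that step to arm. Judgement that leans by arm, or by arm and visit together, would bias the between-arm difference in change in mean daily GI.

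The documents do not allow the size to be computed. With an assumed 20% of carbohydrate coded by judgement and an assumed 5-unit lean in one arm at 3 months, the shift is 1 GI unit (20% of the target). The two-sided error rate then rises from 0.05 to about 0.10 at SD 5 with 23 per arm. With a small share and a small lean the effect is negligible.

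The documents do not support saying that the coder was unmasked or that bias occurred. The change is worth making because it is cheap and removes a route to bias, but the point does not invalidate the design. My confidence is moderate, because an unseen full protocol may already provide masking.

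**What to change.** 1. Pool all foods from both arms and both visits into one de-duplicated list. Remove participant, arm and visit, and keep preparation details in the food description.
2. Have the same dietitian assign one GI value to each food on that list.
3. Lock the food-to-GI table before merging it with the records and the allocation.
4. Report by arm the share of carbohydrate coded by judgement. This supplies the missing input and shows whether the shares differ. If they do, even an error common to both arms would not cancel fully.

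One value per food means that the same food cannot be valued differently by arm or visit. Removing arm labels from whole records would not be enough, since the pattern of foods can still suggest the arm. One limit remains: a food eaten in only one arm is still valued by judgement.

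Any analysis restricted to directly matched foods should be labelled exploratory. It selects on food choices made after randomization, which the intervention aims to change.

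The cost is some data-management work by existing staff and possible loss of record-specific context. The sample size does not change. The article reports that data collection ended in June 2018 and that analysis was completed in December 2018, so this would be a recoding of existing records. If the coding was in fact masked, one sentence in the dietary assessment section settles the point.
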